#### **8-6-4 Study withdrawal assessment**

| Type of Assessment                                                                                              | Timeline - Comments                                   |
|-----------------------------------------------------------------------------------------------------------------|-------------------------------------------------------|
| PHYSICAL EXAMINATION
Gynecological examination
Additional examination left to clinician discretion |                                                       |
| LABORATORY TESTS
- FSH, estradiol, inhibin B and anti-Müllerian hormone (ovarian reserve)             | In case of menstrual disorders or menopausal symptoms |
| - CA-125                                                                                                        | Single assay                                          |

### **8-7 Endpoints**

#### **8-7-1 Pelvic cancer**

The cumulative incidence of pelvic cancer will be estimated by measuring the time-to-onset of pelvic cancer, defined as time from the date of the fimbriectomy to the date of the ovarian cancer, high-grade primary peritoneal cancer, or cancer of other gynecologic pelvic location, with death without pelvic cancer considered a competitive event. Study withdrawal for oophorectomy is also a competitive event. Patients alive without pelvic cancer or oophorectomy based on most recent information are censored at this time.

### ***8-7-2 Occult lesions***

The proportion of occult lesions on the fimbriectomy specimen is defined as the number of intraepithelial serous carcinomatous tubal lesions, and in situ or invasive cancer on the surgical specimen (at the fallopian tube or adjoining ovary fragment).

The proportion of p53 signature foci and proliferative foci (ki67  $\geq$  10%) will also be described.

### ***8-7-3 Incidence or recurrence of breast cancers***

The cumulative incidence of breast cancer or breast cancer recurrence is defined as the time from the date of the fimbriectomy to the date of the breast cancer or recurrence, with death without breast cancer considered a competitive event. Patients alive without pelvic cancer or oophorectomy based on most recent information are censored at this time. A secondary analysis will be performed considering study withdrawal for oophorectomy as a competitive event.

### ***8-7-4 Incidence of secondary oophorectomy and their morbidity***

Their morbidity is also theoretical and very low. It involves possible gastrointestinal or ureteral injury related to the release of adhesions between the remaining ovaries and these structures as well as bleeding from the adnexal pedicle. The greatest risk is actually the development of ovarian cysts on the remaining ovaries, as the theoretical age of menopause approaches. However, this risk is not greater than that of the general population. It is the significance of these cysts in this particular context that should contribute to whether or not specific surgery is indicated. Complications related to secondary oophorectomy will be assessed up to one month post-procedure according to NCI-CTCAE v4.0.

The cumulative incidence of secondary oophorectomy is defined as the time from the date of the fimbriectomy to the date of the oophorectomy, with death without oophorectomy considered a competitive event. Patients alive without pelvic cancer or oophorectomy based on most recent information are censored at this time. The timing of the oophorectomy will also be described: prior to menopause, within 6 months of menopause onset, more than 6 months after menopause.

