| ASSESSMENT CRITERIA            | 
Primary:
 
 
○ The cumulative incidence of pelvic cancer will be estimated by measuring the time-to-onset of pelvic cancer, defined as the time from the date of the fimbriectomy to the date of the ovarian cancer, high-grade primary peritoneal, or other gynecologic pelvic location, with death without pelvic cancer considered a competitive event. Study withdrawal for oophorectomy is also a competitive event. Patients alive without pelvic cancer or oophorectomy based on most recent information are censored at this time.
 
 
Secondary:
 
 
○ Morbidity: post-operative complications up to 30 days post-procedure according to Clavien-Dindo classification (2009), according to NCI-CTCAE v4.0 beyond this time frame
 
○ Histological occult lesions: number of intraepithelial serous carcinomatous tubal lesions, and invasive cancer on the surgical specimen
 
○ Incidence or recurrence of breast cancers: The cumulative incidence of breast cancer or breast cancer recurrence is defined as the time from the date of the fimbriectomy to the date of the breast cancer or recurrence, with death without breast cancer considered a competitive event. Patients alive without breast cancer based on most recent information are censored at this time. A secondary analysis will be performed considering study withdrawal for oophorectomy as a competitive event.
 
○ Incidence of secondary oophorectomies and their morbidity: 
 
○ The cumulative incidence of secondary oophorectomy is defined as the time from the date of the fimbriectomy to the date of the oophorectomy, with death without oophorectomy considered a competitive event. Patients alive without oophorectomy based on most recent information are censored at this time. The timing of the oophorectomy will also be described: prior to menopause, within 6 months of menopause onset, more than 6 months after menopause.
 
○ complications according to NCI-CTCAE v4.0 scale
 
 
 
 |                     |         |                          |                     |               |                     |

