## **6-2 Potential disadvantages of radical fimbriectomy [Greene 2010]**

- The rate of pelvic tumors that develop from the tube is not precisely known, and the benefit for these women will obviously be proportional.
- The idea is to perform castration afterward, closer to the natural age of menopause, and this will require a second pelvic procedure. Some women may not want to consider this second surgery, in the hope of a sufficiently reduced risk by removing the tube.
- The potential drawback that seems most important to us is the lack of reduction in breast cancer risk through ovarian suppression. Castration is generally known to reduce the risk of breast cancer, particularly tumors with steroid receptors. It is more than likely that this risk reduction is through ovarian hormone suppression. The studies confirm this risk reduction for women who have a BRCA1 and BRCA2 mutation [Rebbeck 2009]. However, it should be noted that in prospective studies this reduction in breast cancer risk is greater for BRCA2 mutations than BRCA1, which is not unexpected given the large proportion of tumors without BRCA1 receptors. However, the absence of a receptor may not necessarily reflect complete independence of the tumor from sex hormones. It should also be noted that these studies are observational and subject to risks of bias that are not always easy to identify or correct; therefore, the estimate of breast cancer risk reduction is only approximate [Heermskerk 2010]. One can also argue about the possibility of replacement therapy after castration; however, this treatment is contraindicated in breast cancer and some studies show that this treatment may not be as

effective as natural hormonal impregnation [Rebbeck 2009]. A substantial proportion of women who will be enrolled will likely have a history of BRCA1-related HR- breast cancer and the influence of castration on contralateral cancer risk is not really documented [Domchek 2010].

All of these arguments justify a prospective study of bilateral radical fimbriectomy that may help to better understand the risk-benefit ratio in this complex and very personal choice, but also to better understand the natural history of high-grade pelvic tumors that are obviously not just the prerogative of BRCA 1/2 mutations.

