#### **8-8-2 Statistical analysis**

The statistical analyses will be performed by the Oscar Lambret Center Methodology and Biostatistics Unit (*Unité de Méthodologie et de Biostatistique*, UMB).

The study populations will be as follows:

- The descriptive analysis of baseline characteristics will be performed on the patient population enrolled in the study.
- The descriptive analysis of the procedure, disease, morbidity, and satisfaction questionnaire will be performed on the patient population who underwent radical fimbriectomy.

- The analysis of cumulative incidence of pelvic cancer, breast cancer, and secondary oophorectomy will be performed on the patient population who underwent surgery and excluding patients with invasive cancer or STIC on the fimbriectomy specimen.
- The analysis of secondary oophorectomy complications will be performed on the patient population who underwent oophorectomy secondary to the fimbriectomy.

The statistical analysis of baseline characteristics, procedure, and disease will be essentially descriptive in nature and will be presented in summary tables including the number of missing data. Continuous variables will be summarized by median and extreme values, and mean and standard deviation if warranted. Categorical variables will be presented as contingency tables (absolute frequency and percentage of each modality).

The inclusion and exclusion criteria will be verified from the data recorded in the case report forms. Any protocol deviations will be detailed, as well as the causes of ineligibility and non-evaluability.

The cumulative incidences of pelvic cancer, breast cancer, and secondary oophorectomy will be estimated by the competitive risk method (Kalbfleish [*sic*: Kalbfleisch] and Prentice), as defined in section 8.7 (endpoints).

In secondary analysis, cumulative incidences of pelvic cancer and breast cancer will be estimated based on age reached.

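### The secondary-oophorectomy endpoint does not separate oophorectomy done to treat a pelvic cancer found in follow-up, and its two censoring rules disagree

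*Protocol*

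**What the plan says.** - **Event and competing event.** Section 8-7-4 and the synopsis both measure the "time from the date of the fimbriectomy to the date of the oophorectomy, with death without oophorectomy considered a competitive event". Neither restricts the indication.
- **Censoring.** Section 8-7-4 states: "Patients alive without pelvic cancer or oophorectomy based on most recent information are censored at this time". For the same endpoint the synopsis states: "Patients alive without oophorectomy based on most recent information are censored at this time".
- **Primary endpoint.** Section 8-7-1 sets the opposite direction: "Study withdrawal for oophorectomy is also a competitive event". No matching rule makes pelvic cancer compete with oophorectomy.
- **Withdrawal.** Section 8-5 lists post-fimbriectomy oophorectomy, with one month of follow-up for complications, but not pelvic cancer. Section 8-4 makes invasive cancer or STIC on the fimbriectomy specimen a criterion for early withdrawal.
- **Analysis sets in 8-8-2.** The cumulative incidences are estimated in operated women, "excluding patients with invasive cancer or STIC on the fimbriectomy specimen". The next item carries no such exclusion: "The analysis of secondary oophorectomy complications will be performed on the patient population who underwent oophorectomy secondary to the fimbriectomy".
- **Purpose.** Section 6-2 says of the second step: "The idea is to perform castration afterward, closer to the natural age of menopause".

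**The concern.** Two questions matter for a two-step strategy: how many women come back for the second operation, and what that operation costs them. As written, the endpoint mixes preventive removal of the ovaries with removal as part of treating a pelvic cancer, which is the failure the trial is looking for. The error runs in an awkward direction, because the more often fimbriectomy fails, the higher the reported oophorectomy incidence. Complications related to those operations are pooled with those of preventive surgery, whose morbidity 8-7-4 expects to be very low.

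The censoring conflict is a separate defect. Two analysts, one working from 8-7-4 and one from the synopsis, could handle the same woman differently.

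**Working it through.** The protocol gives no expected rate of secondary oophorectomy, so there is no figure to reproduce. The check follows individual women through the rules and then bounds the size.

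**1. A woman with pelvic cancer at month 24 whose ovaries are removed at cancer surgery at month 25.** At month 24 she is not withdrawn (8-5), not dead, and has no competing event under 8-7-4. At month 25 she meets the event. In the primary analysis she is a pelvic cancer event at month 24; in this analysis she is an oophorectomy event at month 25. She also belongs to the complication set of 8-8-2.

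**2. A living woman with pelvic cancer and ovaries in place.**

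| Rule | Event | Competing event | Censored |
|---|---|---|---|
| 8-7-4 | no | no | no, because she has pelvic cancer |
| Synopsis | no | no | yes, at last information |

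**3. Number of women.** From 8-8-1: pelvic tumours 10% at 10 years without prophylactic surgery, 3% at 3 years, maximum 120 patients.
- 120 × 0.03 = 3.6 women by 3 years
- 120 × 0.10 = 12 women by 10 years

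**4. Effect on oophorectomy incidence.** Constant cause-specific hazards are assumed.
- Cancer hazard: hc = −ln(0.9)/10 = 0.01054 per year. This gives 1 − 0.9^0.3 = 3.1% at 3 years, in line with the protocol's 3%.
- Elective oophorectomy hazard: h2 = 0.02, 0.05 or 0.10 per year. This is an assumption; the protocol gives none.
- Worst case: fimbriectomy has no preventive effect, and every pelvic cancer leads at once to oophorectomy.
- Incidence as written: 1 − exp(−(h2 + hc)T)
- Incidence with pelvic cancer competing: h2/(h2 + hc) × [1 − exp(−(h2 + hc)T)]

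| h2 per year | T (years) | As written | Cancer competing | Difference (points) |
|---|---|---|---|---|
| 0.02 | 3 | 8.8% | 5.7% | 3.0 |
| 0.05 | 3 | 16.6% | 13.7% | 2.9 |
| 0.10 | 3 | 28.2% | 25.5% | 2.7 |
| 0.02 | 10 | 26.3% | 17.2% | 9.1 |
| 0.05 | 10 | 45.4% | 37.5% | 7.9 |
| 0.10 | 10 | 66.9% | 60.5% | 6.4 |

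Differences are taken before rounding.

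**5. Effect on the complication rate.** Pooled rate = (K × 0.031 + c × p)/(K + c), with K elective and c cancer operations. The 3.1% is the postoperative rate in 8-7-5-3 from a series of prophylactic adnexectomies, used here as a proxy for an elective second step. K, c and p = 10% to 30% are assumptions.
- K = 40, c = 4: (1.24 + 0.4)/44 = 3.7% to (1.24 + 1.2)/44 = 5.5%
- K = 80, c = 4: (2.48 + 0.4)/84 = 3.4% to (2.48 + 1.2)/84 = 4.4%
- p = 3.1%: the pooled rate stays at 3.1%, with no inflation

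**The case against.** **The endpoint is called secondary, not planned.** This is correct. Section 8-7-4 foresees surgery for cysts and reports timing relative to menopause, including before it, and 8-7-5-3 foresees earlier oophorectomy after induced menopause. A reader might infer that the protocol sets out to count only planned second-step operations and miscounts them; it never says so. What remains is that treatment of a diagnosed pelvic cancer is not separated from the rest, although 6-2 gives the second step a preventive purpose.

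**Sections 9.4.1 and 9.4.2 keep cancer surgery apart.** They do so only in part. Section 9.4.1 concerns cancer discovered incidentally. It does not address cancer arising in follow-up, and neither section defines the endpoint or an analysis set.

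**Complications are described by relationship to the procedure.** This limits the problem, since complications of other parts of cancer surgery need not be attributed to the oophorectomy. Relationship still does not separate indication: a complication of an oophorectomy done within cancer surgery remains related to that oophorectomy.

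**Women with cancer or STIC on the specimen.** A reader might infer that they inflate the complication table, because 8-8-2 does not repeat their exclusion there. The protocol does not establish this. Section 8-4 withdraws them early, and the one-month complication follow-up is attached to oophorectomy in 8-5, a separate list. Whether their data reach the table depends on what is collected after early withdrawal.

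**Coding by indication can be left to the statistical analysis plan.** That would be fair had the protocol been silent. It fixes the event, the competing event and the censoring itself, and states the censoring in two ways.

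**Conclusion.** The point holds in a limited form. As written, an oophorectomy done to treat a pelvic cancer diagnosed in follow-up is a secondary-oophorectomy event and enters the complication set. The censoring conflict between 8-7-4 and the synopsis follows from the text alone and needs no assumption.

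The effect on incidence is at most about 3 points at 3 years and 6 to 9 points at 10 years. These are upper bounds within the assumed range of elective rates: they take the no-surgery cancer risk and assume that every pelvic cancer leads to oophorectomy. A reader might add the full 10 points of 10-year cancer risk, but women who have already had the ovaries removed cannot contribute a second event.

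A marked inflation of the complication rate is also tempting to infer. The protocol gives no complication rate for cancer surgery and none specific to secondary oophorectomy, so the size is not established. The worked range of 3.7% to 5.5% against 3.1% is only an illustration.

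The endpoint is secondary and descriptive. Neither the sample size nor the stopping rule depends on it.

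**What to change.** In 8-7-4 and the synopsis, use one definition:
- **Event:** oophorectomy before any diagnosis of pelvic cancer, including operations for a cyst or a suspicious test, whatever the histology. A woman operated on for suspicion with a benign result then keeps a status.
- **Competing events:** pelvic cancer diagnosed before oophorectomy, and death without oophorectomy.
- **Censoring:** women alive without pelvic cancer and without oophorectomy, at last information.

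In 8-8-2, restrict the main oophorectomy complication table to these operations. List separately any oophorectomy done to treat a diagnosed pelvic cancer, and any done after invasive cancer or STIC on the fimbriectomy specimen, so far as such data are collected after early withdrawal under 8-4.

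The cost is a change of wording, one indication code per oophorectomy, and slightly fewer events in the oophorectomy tables.

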### ***8-7-5 Postoperative complications***

Morbidity will be assessed:

- up to 30 days post-procedure according to the Clavien-Dindo classification [2009]
- and beyond this time (until confirmation of menopause for patients who have not had a secondary oophorectomy, or up to one month after secondary oophorectomy) according to the NCI-CTCAE v4.0 grading scale.

#### ***8-7-5-1 Adverse event***

An adverse event is any change in the patient's initial state before treatment, including intercurrent diseases, whether or not the event is considered to be related to the products studied and occurring at any time during the study.

***The nature of each adverse event, date of onset, duration, seriousness, relationship to surgery, associated treatments, and outcome will be established. The intensity of adverse events will be graded according to the criteria based on their time to onset (see above).***

#### *8-7-5-2 Serious adverse event*

Not considered a serious adverse event (SAE):

- Hospitalization scheduled prior to the start of the trial and/or planned per protocol (biopsy etc.).
- Definition:

*A serious adverse event (SAE) is any event:*

- Leading to death,
- Life-threatening,
- Leading to hospitalization or prolongation of hospitalization,
- Causing permanent disability or severe temporary disability,
- Causing a birth defect, fetal impairment or abortion,
- Medically significant.

The terms *disability and incapacity* are any temporary or permanent physical or psychological disability that is clinically significant and affects the patient's physical activity and/or quality of life.

Any *medically significant* clinical event or laboratory finding considered serious by the investigator that does not meet the severity criteria defined above. They may pose a risk to the patient and require medical intervention to prevent an outcome corresponding to one of the severity criteria mentioned above (*examples: overdoses, second cancers, pregnancies and new facts that may be considered medically significant*).

Patient death by progression is an expected serious event.

#### *8-7-5-3 Expected serious adverse event (expected SAE)*

An expected SAE is an event already mentioned in the literature data.

Perioperative morbidity from prophylactic laparoscopic adnexectomy is very low. The rates of intraoperative complications were reported at 1.3% and postoperative complications at 3.1% with a **conversion rate to laparotomy** of 0.8% in a series of 159 patients [Kenhuis 2010]. There is no theoretical reason why fimbriectomy has higher levels than this. Apart from the known risks of any laparoscopic procedure, the specific operative morbidity of radical fimbriectomy would be limited to the sole risk of **postoperative bleeding** of the remaining ovaries. An inspection of the ovarian cut section after deflation of the pneumoperitoneum over a few minutes and re-insufflation enables sealing with a few elective bipolar coagulations if necessary.

Later, the **risk of induced menopause** may theoretically be observed if the two sources of blood supply from the ovary (adnexal and infundibulopelvic pedicle) were altered by the procedure. This risk is naturally increased in case of a single adnexa. If menopause is confirmed by the absence of periods

and a hormone panel (LH and FSH plasma estradiol), the additional oophorectomy could be discussed with the patient sooner.

#### *8-7-5-4 Unexpected serious adverse event (unexpected SAE)*

An unexpected SAE is an event that is not mentioned or different in nature, intensity, or progression from what is described above.

#### *8-7-5-5 Intensity criteria*

The intensity criterion should not be confused with the severity criteria, which serve as a guide for defining reporting obligations.

The intensity of events will be estimated according to the Clavien-Dindo and NCI-CTC version 4.0 (grade 1 to 5 toxicity) classifications.

The intensity of adverse events not listed in this classification will be assessed according to the following qualifications:

|                        |                                                    |
|------------------------|----------------------------------------------------|
| Mild (Grade 1):        | does not affect the patient's usual daily activity |
| Moderate (Grade 2):    | interferes with the patient's usual daily activity |
| Severe (Grade 3):      | prevents the patient's usual daily activity        |
| Very Severe (grade 4): | imposes resuscitation measures/life-threatening    |
| Death (Grade 5)        |                                                    |

#### *8-7-5-6 Action plan*

The investigator informs the Sponsor of all Expected Serious Adverse Events (expected SAE) and Unexpected Serious Adverse Events (unexpected SAE), whether or not they are attributable to the research, that occur during the study or within 30 days after the fimbriectomy.

All delayed Serious Adverse Events (occurring after this 30-day period) considered as being reasonably related to the research must be reported without time limitation.

**The notification is made by email using the "*Serious Adverse Event Notification*" form recorded as accurately as possible, signed and dated.**

